### Sample size

The power calculation is based on bone loss data in a randomized study on mandibular overdentures [37] similar to the present study. Delayed loaded regular-diameter implants of 15 patients showed bone loss of 0.51 ± 0.39 mm after one year and of 0,62 ± 0.44 mm after 3 years. Immediate loaded implants of 15 patients showed bone loss of 0.91 ± 0.63 mm after 1 year and 0.98 ± 0.64 mm after 3 years. A sample size of 26 in each group will have 80 % power to detect a difference in means of 0.4 (the difference between a group 1 mean of 0.9 and a group 2 mean of 0.5) assuming that the common standard deviation is 0.5 using a two group t-test with a 0.05 two-sided significance level. Considering response rate of 75 %, a total of 80 patients (40 per group) should be allocated to the trial.

### Randomization and blinding

The randomization was performed centrally by the trial statistician based on a sequence of computer-generated numbers with a 1:1 allocation ratio stratified by jaw (maxilla, mandible) and study center.

Due to the apparent treatment differences, it is not possible to blind the dentists, clinical investigator, and/or the participating patient. However, the two examiners of the radiographs and the statistician will be blinded.

### Data management

The data of the paper case report forms will be entered in the electronical spreadsheet by assistants of the leading study site. Non-numeric data will be coded not only for statistical analyses but also to identify missing or erroneous values by range checks. The cases are pseudonymized (continuously counted according to a single main list). Each participating center got an identification number (ID-CENTER). Subjects included in the cohort got a pseudonym (ID-PROBAND) by the participating center. The centers are the keyholders for the patients’ personal data. The list of pseudonyms and patients´ ID will be listed in a special file. Only the head of the department in the dental school (keyholder) could open the pseudonyms. The principal investigator will have access to the cleaned dataset. Other members of the research group will be given access to data for analyses and publication by request.

Participant forms will be stored in locked office cabinets. The case report forms will be archived for 15 years after study closure. A member of our board of the community medicine research net with expertise in statistical methodology will guarantee the abidance of randomization and quality assurance at the data acquisition and data base. Every 12 months the member and the sponsor will forward interim reports without any analyses.

### Statistical methods

Because of the statistical power, we choose the continuous variable bone level to be the primary outcome measure. We differentiate confirmatory and exploratory analyses. Confirmatory analysis is related to differences between groups whereas exploratory analysis is related to the rate of change between groups (interaction between time and group), which yields low power test herein. However, we present the joint test of the factor group and the interaction between time and group. The explanations of the variables are outlined in Table 2.

**Table 2 Tab2:** Variables, measures, hypotheses, and methods of analysis

Variable	Measure, parameterization	Variable name for syntax	Level	Hypothesis	Points in time	Methods of analysis: Stata command (version 14)
1. Primary outcome						
a) Bone level	Radiographic bone levels around implants (mesial, distal, mm, continuous)	Bone level	Implant	Group A will show more bone loss than group B	(t_0_), t_4_, t_6_	Mixed model for continuous responses: mixed
2. Secondary outcome: Implant success	Modified criteria of Albrektsson (binary): composite variable on implant level	Success	Implant	Group A will show less success than group B	t_4_, t_6_	Mixed model for binary responses: melogit
a) Related to infection	Modified sulcus bleeding index (0–3 on 2 sites per implant)	SBI	Implant		t_1_, t_2_, t_3_, t_4_, t_5_, t_6_	Mixed model for ordinal responses: meologit
	Bleeding on probing (binary on 4 sites per implant)	BOP	Implant		t_1_, t_2_, t_3_, t_4_, t_5_, t_6_	Mixed model for binary responses: melogit
b) Clinical immobility	Clinical immobility of the implant (binary)	Mobility	Implant		t_1_, t_2_, t_3_, t_4_, t_5_, t_6_	Mixed model for binary responses: melogit
c) Pain	Persistent pain or discomfort (binary)	Pain	Implant		t_1_, t_2_, t_3_, t_4_, t_5_, t_6_	Mixed model for binary responses: melogit
d) Radiolucency	Evidence of peri-implant radiolucency (binary)	XLucency	Implant		t_4_, t_6_	Mixed model for binary responses: melogit
e) Survival	Implant in situ (binary)	ImplantLoss	Implant		Continuous time	Kaplan-Meier
3. Tertiary outcome						
a) Periodontal and periimplant conditions	Probing depths (mm, continuous on 4 sites per implant)	ProbingDepth	Implant	Group A will show higher values than group B	t_1_, t_2_, t_3_, t_4_, t_5_, t_6_	Mixed model for continuous responses: mixed
	Probing depths (mm, continuous on 4 sites per tooth)	ProbingDepth	Tooth	Overall improvement at teeth, improvement occurred faster in group A than in group B	t_1_, t_2_, t_3_, t_4_, t_5_, t_6_	Mixed model for continuous responses: mixed
	Osstell (0–100, continuous on implant level)	Osstell	Implant	Group A will show lower values than group B until the fourth month, thereafter equalization between A and B	t_1_, t_2_, t_3_, t_4_, t_5_, t_6_	Mixed model for continuous responses: mixed
	Periotest (−8.0 - +50.0, continuous on tooth level)	Periotest	Tooth	Overall improvement at teeth, improvement occurred faster in group A than in group B	t_1_, t_2_, t_3_, t_4_, t_5_, t_6_	Mixed model for continuous responses: mixed
	Periotest (−8.0 - +50.0, continuous on implant level)	Periotest	Implant	Group A will show higher values than group B until the fourth month, thereafter equalization between A and B	t_1_, t_2_, t_3_, t_4_, t_5_, t_6_	Mixed model for continuous responses: mixed
b) Oral health related quality of life	OHIP-G14 questionnnaire (0–56, continuous)	OHIP	Patient	Overall improvement, improvement occurred faster in group A than in group B	t_1_, t_2_, t_3_, t_4_, t_5_, t_6_	Mixed model for ordinal responses: meologit
c) Patient’s satisfaction with the PRDP	Questionnnaire 8 items (Five-point Likert-scale, 8–40 continuous)	Satisfaction	Patient	Overall improvement, improvement occurred faster in group A than in group B	t_1_, t_2_, t_3_, t_4_, t_5_, t_6_	Mixed model for ordinal responses: meologit
d) Nutrition of the patients	Food frequency questionnaire (1–7)	FFQ	Patient	Overall improvement, improvement occurred faster in group A than in group B	t_1_, t_2_, t_3_, t_4_, t_5_, t_6_	Mixed model for ordinal responses: meologit
	Food avoidance questionnaire (binary)	FAQ	Patient	Overall improvement, improvement occurred faster in group A than in group B	t_1_, t_2_, t_3_, t_4_, t_5_, t_6_	Mixed model for binary responses: melogit
e) Chewing efficiency	Colour-mixing ability test with two coloured chewing gum (continuous)	Chewing	Patient	Overall improvement, improvement occurred faster in group A than in group B	t_1_, t_2_, t_3_, t_4_, t_5_, t_6_	Mixed model for ordinal responses: meologit
4. Exposure						
Group	2 categories		Jaw		t_0_	
5. Time variables						
TimePoint	0-6 for outcomes				0-6 for t_0_ –t_6_	
Week	Time [weeks]		Patient		Week	
SqrtWeek	Square root of week		Patient		Root of week	
Time			Patient		Continuous	
6. Confounder						
Age	Restricted cubic splines with 3 knots (2 coefficients)	Age	Patient		t_−1_	
Gender	2 categories (men; women)	Gender	Patient		t_−1_	
Center	4 categories	Center	Patient		t_−1_	
Jaw class	4 categories	JawClass	Jaw		t_−1_	
Jaw	2 categories (upper; lower)	Jaw	Jaw		t_−1_	
Tooth	1-16 within jaw	Tooth	Tooth		t_−1_	
Site	Up to 4 sites	Site	Site			
Smoking	3 categories (never; ex; current)	Smoking	Patient			
School education	3 categories (<10, 10, >10 years)	Education	Patient		t_−1_	
Probing depth	Restricted cubic splines with 3 knots (2 coefficients)	ProbingDepth0	Tooth		t_−1_	
Bone level	Before treatment in groups	BoneLevel0			t_0_	
Periotest	Restricted cubic splines with 3 knots (2 coefficients)	Periotest0	Tooth		t_−1_	
OHIP-G14 questionnnaire (0–56, continuous)	Restricted cubic splines with 3 knots (2 coefficients)	OHIP0	Patient		t_−1_	
Questionnnaire 8 items (Five-point Likert-scale, 8–40 continuous)	Linear term only	Satisfaction0	Patient		t_−1_	
Food frequency questionnaire (1–7)	Linear term only	FFQ0	Patient		t_−1_	
Food avoidance questionnaire (binary)		FAQ0	Patient		t_−1_	
colour-mixing ability test with two coloured chewing gum (continuous)	Linear term only	Chewing0	Patient		t_−1_	
7. Subgroup analysis						
Jaw class 0 vs 1-3	Secondary outcomes	JawClass		Improvement in group A is better than in group B	t_−1_	
8. Additional analysis						
Maxilla vs. mandible	All outcomes			Maxilla will show less success and more bone loss than mandible; Implant stability (Periotest, Osstell) is lower in the maxilla than in the mandible; no differences in the improvement of other secondary outcomes	t_−1_	

t_1_: 0.5 months; t_2_: 4 months; t_3_: 4.5 months; t_4_: 12 months; t_5_: 24 months; t_6_: 36 months

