**Fig. 4 Fig4:**
[figure not shown]
Organization chart of the trial

Tertiary outcomes arePeriodontal and peri-implant conditions (probing depths, bleeding on probing (BOP), modified plaque index, modified sulcus bleeding index (mod. SBI), tooth and implant mobility measured by Periotest and Osstell)Oral health related quality of life (measure: short German version of the oral health impact profile (OHIP-G14) [33] and Patient’s satisfaction with the PRDP (Likert scale: totally satisfied - not at all satisfied) [34]Food frequency and avoidance questionnaire will be completed by the patients to evaluate the nutrition of the patients [35]Chewing efficiency will be quantified with colour-mixing ability test using a two coloured chewing gum (optoelectronical.evaluation of the ratio of unmixed colour pixels to the total pixel number in a fixed size template) [36]Dental and prosthetic complications: tooth loss, caries, endodontic treatment, implant- or tooth fracture, prosthesis fracture, loss of retention, housing detachments, loss of O-rings.

We hypothesized that after the placement of MDIs there will be significant improvements only in group A and not in group B at the baseline and at the 4- month follow-up examination. After the pick-up of the housings in group B there will be also significant improvements for patients of this group.

Examinations for all secondary outcomes are scheduled before implant placement (pre-treatment, exclusively outcomes No.1- 4), 14 days after implant placement (baseline) and 4, 12, 24 and 36 months after implant placement (Fig. 4). In addition, patients whose housings are picked-up after 4 months will be examined 14 days after the pick-up. A trained examiner of the leading treatment center not involved in the treatment of participants will perform all examinations. Additionally, a second examiner will survey the bone levels at implants on the radiographs.

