### Secondary outcomes

To avoid false positive conclusions, we state a priority ordering in advance [44] based on information on scale (continuous/ordinal/binary), number of time points, level (site/tooth/jaw/patient), and expected number of events (see Table 2).

For six time points, we allow for nonlinear change. The nonlinear change is modelled by taking the square root of time [45] because we expect a higher rate of change in the first weeks. The confirmatory and the exploratory SBI model:

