### Tertiary outcomes

See Table 2 for priority ordering. We allow for nonlinear change as described above. If possible we adjust for values before treatment [40, 43]. The confirmatory and the exploratory model of periotest for teeth:

For tertiary outcomes other than periodontal or peri-implant conditions, we expect differences between groups before housing in group B (time points t_1_ and t_2_) but no differences after that (time points t_4_-t_6_). Thus, we present only confirmatory analyses. The model for food frequency questionnaire at time points t_1_ and t_2_:

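### Osstell and implant Periotest: the confirmatory group effect does not isolate the early difference that Table 2 predicts, and the 4.5-month visit is attended selectively in arm A

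*Protocol article*

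**What the plan says.** Table 2 of the protocol article (Statistical methods) gives the Osstell hypothesis as "Group A will show lower values than group B until the fourth month, thereafter equalization between A and B" and the implant Periotest hypothesis as "Group A will show higher values than group B until the fourth month, thereafter equalization between A and B". Both rows list all six visits, timed as "t_1_: 0.5 months; t_2_: 4 months; t_3_: 4.5 months; t_4_: 12 months; t_5_: 24 months; t_6_: 36 months".

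The opening of Statistical methods sets the roles: "Confirmatory analysis is related to differences between groups whereas exploratory analysis is related to the rate of change between groups". It continues: "However, we present the joint test of the factor group and the interaction between time and group". It does not say whether that joint test is confirmatory or exploratory.

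For outcomes measured six times, the Secondary outcomes section states: "For six time points, we allow for nonlinear change", using the square root of time. The Tertiary outcomes section carries this over. It then says: "For tertiary outcomes other than periodontal or peri-implant conditions, we expect differences between groups before housing in group B", that is, at t1 and t2, with none expected at t4 to t6. The food frequency questionnaire is accordingly modelled at t1 and t2. No such limit is given for Osstell or Periotest.

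On t3, the Outcomes section says that "patients whose housings are picked-up after 4 months will be examined 14 days after the pick-up". Under Interventions, that covers every arm B patient by design. In arm A it covers only patients with at least one implant in the study jaw below 35 Ncm, who first receive a soft reline.

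**The concern.** A difference that is present until month 4 and then disappears is a group-by-time interaction. The plan calls that interaction exploratory and reserves the confirmatory label for the group effect. Averaged over six visits, the group effect mixes two visits where a difference is predicted with four where none is. The plan limits the visits for the patient-level tertiary outcomes, where it expects the same early-only pattern, but leaves these two rows out of that limit. A null six-visit result could then be misread as evidence against the early difference.

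The second matter is t3. Table 2 lists it like any other visit, although arm A patients attend it only if their insertion torque was low. Torque plausibly bears on implant stability, which Osstell and Periotest measure. It appears neither among the confounders in Table 2 nor in the adjustment sets under Primary outcome: bone level.

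**Working it through.** **1. The plan's own power figure.** The protocol gives no power for Osstell or Periotest. Its one figure, for bone level, reproduces: difference 0.4 and SD 0.5 give a standardised difference of 0.8. At two-sided 0.05 and 80 % power, the t-test needs 25.5, so 26 per group (power 0.807 at 26). With 40 allocated per group and a 75 % response, 40 × 0.75 = 30 per group are evaluable. The check below borrows 0.8 SD and 30 per arm as illustrations.

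**2. Dilution.** Let the true contrast be d at t1 and t2 and 0 at t3 to t6.
- Everyone attends t3: the six-visit group effect is 2d/6 = 0.33d, a 3.0-fold dilution.
- No arm A patient attends t3, visit as a factor: 2d/5 = 0.40d, 2.5-fold.
- Same, with square root of week as the time term: 0.42d, 2.4-fold.
- Half of arm A attends t3: 0.36d (visit factor) or 0.38d (square root of week).

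The range is 0.33 to 0.42, or 2.4- to 3.0-fold.

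**3. Power.** Assume one value per patient and visit, and a common within-patient correlation ρ. The mean of k visits has variance ρ + (1 − ρ)/k in SD² units, and the group difference has SE = √{(2/30)[ρ + (1 − ρ)/k]}.

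Example, ρ = 0.3:
- t1 and t2: SE = √(0.0667 × 0.65) = 0.208; 0.8/0.208 = 3.84; power Φ(3.84 − 1.96) = 0.97.
- Six visits, full attendance: effect 0.8/3 = 0.267; SE = √(0.0667 × 0.417) = 0.167; ratio 1.60; power 0.36.

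The other entries come from the expected generalised least squares coefficient under the same correlation structure.

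| ρ | Group effect, t1 and t2 | Six visits, all of A at t3 | Six visits, none of A at t3, square root of week | Joint test, six visits (all / none of A at t3) |
|---|---|---|---|---|
| 0.3 | 0.97 | 0.36 | 0.52 | 0.89 / 0.97 |
| 0.5 | 0.95 | 0.27 | 0.40 | 0.95 / 0.99 |
| 0.7 | 0.92 | 0.22 | 0.33 | 0.99 / over 0.99 |

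**4. Selection at t3.** Torque is measured before the envelope is opened, so randomisation balances it in expectation. The t3 attendance rule undoes that balance. If a share q of arm A is low-torque and differs from the rest of A by D SD in stability, the raw A versus B contrast at t3 shifts by (1 − q)D with no loading effect. The protocol gives neither q nor D. For q from 0.25 to 0.75 and D from 0.5 to 1.0, the shift runs from 0.25 × 0.5 = 0.13 SD to 0.75 × 1.0 = 0.75 SD. The bias in a mixed model is smaller, because the random effects also use those patients' other visits.

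**The case against.** The strongest reply is the joint test of group and group-by-time. A fading difference is what it can detect, and its power under the same assumptions is 0.89 to over 0.99. A reader might infer that the early difference would probably be missed altogether. The protocol does not support that, because the loss concerns the group effect alone. What remains is that the joint test has no stated status, does not estimate the difference up to month 4, and does not remove the selection at t3.

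Second, the model content is inferred. The syntax is not shown, the only Periotest model announced is the one for teeth, and Table 2's visit column is not decisive: the food frequency row also lists t1 to t6 but is modelled at t1 and t2. This stands. The six-visit reading rests on the Tertiary outcomes section leaving peri-implant conditions out of its t1 and t2 limit.

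Third, equalisation may be gradual. Some difference remaining at t3 or later would make the dilution smaller than calculated.

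Fourth, a reader might extend the dilution to every six-visit model. Implant probing depth has a hypothesis with no time limit, and bleeding index, bleeding on probing, mobility and pain have no row-specific one. The tooth-level rows, which predict faster improvement in A, share the problem only loosely.

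Fifth, it is tempting to call the arm A patients at t3 a poor-bone subset, or to say that most of A never had a month-4 pick-up. The protocol links poor bone quality to torque below 15 Ncm, which leads to exclusion. One implant below 35 Ncm sends the whole jaw to soft relining, so that subset may include high-torque implants. Its share of arm A is not given.

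**Conclusion.** The point holds for two tertiary rows. For Osstell and implant Periotest, the effect labelled confirmatory does not match the stated hypothesis. If all six visits enter, it recovers 0.33 to 0.42 of the early contrast, with power of about 0.22 to 0.52 instead of 0.92 to 0.97. These figures assume 0.8 SD, 30 per arm, a patient-level outcome, correlation 0.3 to 0.7 and no difference from t3 on. A flat three-fold dilution would require all of arm A to attend t3, which the visit schedule rules out unless every arm A patient had a low-torque implant.

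The t3 point is separate and reaches every six-visit between-group comparison that uses that visit: attendance in A is selected on torque, and torque is not adjusted for. The model-based bias is probably small and cannot be sized from the protocol.

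Severity is low. Bone level and composite implant success are analysed at t4 and t6 and are untouched.

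**What to change.** For Osstell and implant Periotest, name the group contrast over t1 and t2 as the confirmatory analysis, as already done for the food frequency questionnaire. Report t4 to t6 separately, with confidence intervals, to address the predicted equalisation. State whether the joint test is confirmatory or supportive.

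Leave t3 out of the between-group models of all six-visit outcomes (bleeding index, bleeding on probing, mobility, pain, probing depth, Osstell, Periotest) and use it only to describe change after pick-up.

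The cost is a change of wording and model syntax, with no new data. The price is that t3 records no longer contribute to group contrasts.

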### Primary outcome: bone level

Because jaw was used for randomization, we extend Gilthorpe’s mixed model by inserting jaw to levels for patient, tooth, and site [38] and adjust for model complexity by using the Kenward-Roger correction [39]. To ensure hierarchical levels, tooth positions within each jaw are coded from 1 to 16 instead of from 1 to 32 on patient level. The first adjustment set consists of risk factors of periodontal disease including age, gender, and smoking [40]; and design variables including centre, jaw [41], jaw classification, and time. Because X-ray at t_0_ is assessed before differentiating treatment in groups, it is a baseline measurement which can additionally be used to increase efficiency [42]. Note also the discussion on pages 158–160 in Harrell’s textbook [43]. The syntax of the basic confirmatory model with the highest statistical power for the factor group is (Stata’s version 14):

Here, only the time points t_4_ and t_6_ are used as dependent variable (Table 2). To interpret changes after 12 and 36 months in exploratory analyses, we include t_0_ as dependent variable:

In sensitivity analyses, we allow for continuous time instead of points in time, for correlated random effects, or for random effects of other than tooth level and suspend the Kenward-Roger correction. In the second adjustment set, jaw classification is replaced by patient’s mean probing depth before randomization; in the third and fourth set, school education will be added to the first and second set, respectively.

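### Table 2 types chewing efficiency as continuous but assigns it the ordinal model `meologit`, which leaves its group test without the small-sample correction used for bone level

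*Protocol article*

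**What the plan says.** Protocol article, Table 2, part 3 (tertiary outcomes):

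| Row | Scale as stated | Model assigned | Form of the pre-treatment value (part 6) |
|---|---|---|---|
| 3a probing depth, Osstell, Periotest | continuous | "Mixed model for continuous responses: mixed" | splines (probing depth, Periotest) |
| 3b quality of life | "OHIP-G14 questionnnaire (0–56, continuous" | "Mixed model for ordinal responses: meologit" | splines |
| 3c satisfaction | "Questionnnaire 8 items (Five-point Likert-scale, 8–40 continuous" | same as 3b | linear term |
| 3e chewing | "Colour-mixing ability test with two coloured chewing gum (continuous" | same as 3b | linear term |

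The Outcomes section defines chewing efficiency as the share of pixels that remain unmixed in a fixed template. No reason is given for the different model.

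Under the primary outcome, the plan says it will "adjust for model complexity by using the Kenward-Roger correction". The adjustment set is also defined there: "The first adjustment set consists of risk factors of periodontal disease including age, gender, and smoking", plus centre, jaw, jaw classification and time. For tertiary outcomes the text adds "If possible we adjust for values before treatment". For those that are not periodontal or peri-implant, it expects a group difference only at t1 and t2 (0.5 and 4 months). The model syntax is missing from the text at hand.

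**The concern.** The table contradicts itself on scale and model, most plainly in row 3e. The same measurement is a linear covariate before treatment and an ordinal response afterwards.

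The choice also affects the test. Kenward-Roger belongs to linear mixed models. A row that names `meologit` cannot use it and falls back on a large-sample z-test of a factor randomised at patient level, in a trial of about 80 patients. If many covariates are carried along, that test can reject too often and its confidence interval is too narrow. The effect is a conditional odds ratio, which cannot be read in mixing units. Chewing function, quality of life and satisfaction are named in the study aims, which expect faster improvement under immediate loading.

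**Working it through.** **Inputs from the protocol.** 80 patients allocated (Sample size); two visits, t1 and t2 (Tertiary outcomes); two-sided 5 % level (Sample size, Additional notes); covariate coding from Table 2, part 6. The plan states no error rate for these tests beyond the nominal 5 %, so there is no figure of its own to reproduce.

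**Assumed.** Within-patient correlation of about 0.6, outcome distributions, covariate frequencies, and which covariates enter the tertiary models.

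**Step 1: size of an uncorrected test, by formula.** For a patient-level factor with balanced visits, the linear mixed-model test is a regression on n patient means with k coefficients. Maximum likelihood divides the residual sum of squares by n instead of n − k. A z-test therefore rejects when |t| on n − k degrees of freedom exceeds 1.96 × √((n − k)/n).

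- Full set plus Chewing0: k = 1 intercept + 1 group + 1 Chewing0 + 2 age + 1 gender + 2 smoking + 3 centre + 1 jaw + 3 jaw class = 15. For n = 80: 1.96 × √(65/80) = 1.767, size 8.2 %.
- Centre, jaw and Chewing0: k = 1 + 1 + 1 + 3 + 1 = 7. Then 1.96 × √(73/80) = 1.872, size 6.5 %.
- Chewing0 only: k = 3. Then 1.96 × √(77/80) = 1.923, size 5.8 %.

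**Step 2: simulation of the ordinal model under no group effect.** Random-intercept cumulative logit, Wald z, two visits, 2,000 or 4,000 runs per cell (Monte Carlo standard error about 0.4–0.6 points). Two values in a cell are two separate runs. The last column is the exact t-test that Kenward-Roger gives in this balanced case.

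| 80 patients | Ordinal, z | Linear ML, z | Linear, t |
|---|---|---|---|
| Chewing, full set + pre-treatment | 7.8 / 8.5 % | 7.4 / 8.2 % | 4.2 / 5.0 % |
| OHIP, full set + pre-treatment | 7.7 / 8.7 % | 8.4 / 8.3 % | 4.5 / 5.0 % |
| Satisfaction, full set + pre-treatment | 7.6 / 8.2 % | 7.2 / 8.1 % | 4.1 / 4.9 % |
| Food frequency (1–7), full set + pre-treatment | 7.3 % | 8.0 % | 4.8 % |
| Satisfaction, pre-treatment only | 4.9 / 5.6 % | 5.0 / 5.5 % | 4.3 / 4.8 % |
| OHIP, pre-treatment only | 5.0 % | 5.7 % | 4.6 % |

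Chewing with the pre-treatment value only was obtained at 60 patients (5.5 %), not at 80. With group and time alone, chewing and satisfaction gave about 6.3 % at 80. With 60 patients and the full set, the ordinal test gave 10.0–10.8 % for chewing, OHIP and satisfaction.

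A separate simulation (1,000–3,000 runs, standard error 0.5–0.9 points) gave 8.7–9.1 % at 80 patients with the full set, and 6.4–7.3 % with centre, jaw and pre-treatment value. Its linear model with t reference held 4.9–5.5 % with the full set.

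**Step 3: cause.** The uncorrected linear model inflates about as much as the ordinal one, and so, slightly less, does the properly ordinal food-frequency score. The number of categories is not the driver. Chewing has 2 × 80 = 160 observations and so up to 159 cut-points, yet the separate simulation gave 9.0 % with 160 distinct values and 8.7 % with about 27 levels. What matters is the z reference with many coefficients in few patients. Within the linear model most of the repair comes from restricted maximum likelihood (4.6–5.4 % with z at 80 patients, full set); the t reference covers the rest.

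**The case against.** A cumulative-logit model is a valid rank-type analysis. OHIP and satisfaction are bounded questionnaire totals, satisfaction being the sum of eight five-point items, so the ordinal choice there is reasonable and the word continuous may be the loose part. This stands for rows 3b and 3c. It is weaker for a pixel ratio.

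The adjustment set is defined under bone level and justified by periodontal risk factors. For tertiary outcomes the visible text promises only the pre-treatment value, and with that alone the test is close to nominal. This stands too, and is why the size must be given as a range. Against it, Table 2 has a single confounder list that holds age, gender, centre, jaw, jaw class and smoking together with OHIP0, Satisfaction0 and Chewing0, and the Discussion says multivariate analyses will be adjusted for centre. Carrying more covariates over is therefore plausible.

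A reader might infer that these tests simply run at 9–10 %. The documents do not support that. The upper figures need the full set and about 60 patients, and 60 is 80 × 0.75, the planned response over the whole 36-month study. Such a loss by month 4 is not planned for.

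Finally, the article condenses a fuller plan, and it promises further model checks and sensitivity analyses in general terms. But the command for each row is fixed in Table 2, so the mismatch is stated, not omitted.

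**Conclusion.** The mismatch in row 3e is real and unexplained; rows 3b and 3c share it in a milder, defensible form. With about 80 patients at t1 and t2, the named model gives a type I error of about 8–9 % under the full first adjustment set plus pre-treatment value, about 6–7 % with centre, jaw and pre-treatment value, and about 5–6 % with the pre-treatment value only. These figures rest on the assumed correlation, distributions and covariate set, and on complete visits.

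Two stronger readings do not hold. Treating the scores as ordinal is not itself the source of the inflation. Nor are the trial's main conclusions at risk: the plan calls these comparisons confirmatory, but under Statistical methods that word separates group differences from time-by-group interactions. The outcomes remain tertiary, below bone level and implant success.

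**What to change.** In row 3e, replace `meologit` by `mixed` with the Kenward-Roger correction, adjust for Chewing0, and report a mean difference with its confidence interval. Keep the ordinal model as a sensitivity analysis. Name the correction in the cell: `mixed` fitted by maximum likelihood with a z-test would leave 7.4–8.2 % for chewing at 80 patients with the full set.

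For rows 3b and 3c, reconcile scale and model in one of two ways: make the same change, or keep `meologit`, say why, and take the p-value from a re-randomisation test within centre-by-jaw strata, which match the stratified allocation.

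The cost is one table cell for chewing and at most three in all, with no new data. The downside is small: the linear model relies on approximate normality of group means. With skewed OHIP-like scores its simulated error was 5.2–5.5 %.
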